## 5. ANALYSIS POPULATIONS

Analysis sets for the pooled and interim analyses are defined in [Table 3](#). The groups/participants meeting any of the conditions below will be excluded from all analysis sets (unless otherwise indicated) regardless if they meet the definition in [Table 3](#).

- Groups without randomization (eg, group 3 of COV001, group 11 of COV002);
- Participants previously vaccinated with a ChAdOx1 vectored vaccine (eg, group 11 of COV002);
- Participants with HIV diagnosed at study start (group 3 of COV005 and group 12 of COV002).
- Children (< 18 years old)

Furthermore, only groups evaluated for efficacy in COV002 (ie, groups 4, 6, 9,10) will be considered in populations for efficacy analysis.

The corresponding control group for group 2d in COV001 is group 2e.

All analyses will be performed by actual treatment received. For primary endpoint, a sensitivity analysis by randomized treatment assignment will be performed.

Table 3 Populations for Analysis

| Population                    | Description                                                                                                                                                                                                                                                                                                                                                                                                                                                                                                                                                                                            |
|-------------------------------|--------------------------------------------------------------------------------------------------------------------------------------------------------------------------------------------------------------------------------------------------------------------------------------------------------------------------------------------------------------------------------------------------------------------------------------------------------------------------------------------------------------------------------------------------------------------------------------------------------|
| All participants analysis set | All participants screened for the studies, to be used for reporting disposition and screening failures.                                                                                                                                                                                                                                                                                                                                                                                                                                                                                                |
| Any Dose for Safety           | All randomized adult participants who received at least 1 dose of study intervention (AZD1222 or control).
Participants who withdraw consent or assent to participate in the study will be included up to the date of their study termination.
Erroneously-treated participants (eg, those randomized to treatment A but are actually given treatment B) are accounted for in this analysis set by assigning them to the treatment they actually received. A participant who received at least one dose of AZD1222 is classified as AZD1222. This analysis set will be used for safety analysis. |
| Any Dose for Efficacy         | All participants in Any Dose for Safety but for groups in COV002, only efficacy groups (ie, groups 4, 6, 9,10) will be considered.
This analysis set will be used for efficacy analysis.                                                                                                                                                                                                                                                                                                                                                                                                            |
| Dose1 SD for Safety           | Only participants who received SD as the first dose of AZD1222 or in corresponding control group in Any Dose for Safety. The treatment assignment will follow the same rule of Any Dose for Safety analysis set. This analysis set will be used for safety analysis.                                                                                                                                                                                                                                                                                                                                   |

Table 3 Populations for Analysis

| Population                                | Description                                                                                                                                                                                                                                                                                                                                                                                                                                                                                                                                                                                                                                                                                                  |
|-------------------------------------------|--------------------------------------------------------------------------------------------------------------------------------------------------------------------------------------------------------------------------------------------------------------------------------------------------------------------------------------------------------------------------------------------------------------------------------------------------------------------------------------------------------------------------------------------------------------------------------------------------------------------------------------------------------------------------------------------------------------|
| Dose1 SD Seronegative for Efficacy        | 
Only participants seronegative at baseline in Any Dose for Safety who received SD as the first dose of AZD1222 or in corresponding control group, and remain on-study 22 days after their first dose without having had a prior SARS-CoV-2 virologically-confirmeda COVID-19 infection. In addition, for groups in COV002, only efficacy groups (ie, groups 4, 6, 9,10) will be considered.
 
The treatment assignment will follow the same rule of Any Dose for Safety analysis set. This analysis set will be used for efficacy analysis.
                                                                                                                                           |
| SDSD + LDSD Seronegative for Efficacy     | 
Only participants seronegative at baseline in Any Dose for Safety who received LD/SD or SD/SD or in the corresponding control group, and remain on-study 15 days after their second dose without having had a prior SARS-CoV-2 virologically-confirmeda COVID-19 infection. In addition, for groups in COV002, only efficacy groups (ie, groups 4, 6, 9,10) will be considered.
 
The treatment assignment will follow the same rule of Any Dose for Safety analysis set. This analysis set will be used for the efficacy analysis.
                                                                                                                                                   |
| SDSD + LDSD Seronegative ITT for Efficacy | 
Only participants seronegative at baseline in Any Dose for Safety who received two doses, planned to receive LD/SD or SD/SD or in the corresponding control group, and remain on-study 15 days after their second dose without having had a prior SARS-CoV-2 virologically-confirmeda COVID-19 infection. In addition, for groups in COV002, only efficacy groups (ie, groups 4, 6, 9,10) will be considered.
 
Participants will be analysed according to their randomized treatment irrespective of whether they have prematurely discontinued, according to the intent-to-treat principle.
 
This analysis set will be used for the sensitivity analysis of primary endpoint.
 |
| SDSD Seronegative for Efficacy            | 
Only participants seronegative at baseline in SDS + LDSD Seronegative for Efficacy analysis set who received SD/SD or in the corresponding control group, and remain on-study 15 days after their second dose without having had a prior SARS-CoV-2 virologically-confirmeda COVID-19 infection.
 
The treatment assignment will follow the same rule of Any Dose for Safety analysis set. This analysis set will be used for the efficacy analysis.
                                                                                                                                                                                                                                  |

Table 3 Populations for Analysis

| Population                      | Description                                                                                                                                                                                                                                                                                                                                                             |
|---------------------------------|-------------------------------------------------------------------------------------------------------------------------------------------------------------------------------------------------------------------------------------------------------------------------------------------------------------------------------------------------------------------------|
| SDSD + LSDSD for Immunogenicity | Only participants in Any dose for Safety who received LD/SD or SD/SD of AZD1222 or in corresponding control group. Participants without at least one post baseline immunogenicity result will be excluded.

The treatment assignment will follow the same rule of Any dose for safety analysis set. This population will be used for the immunogenicity analysis. |
| SDSD for Immunogenicity         | Only participants in Any Dose for Safety who received two SDs of AZD1222 or in corresponding control group. Participants without at least one post baseline immunogenicity result will be excluded.

The treatment assignment will follow the same rule of Any dose for safety analysis set. This analysis set will be used for immunogenicity analysis.          |

a Virologically-confirmed from RT-PCR or other nucleic acid amplification test.

ITT = intent-to-treat; LD = low dose; RT-PCR = reverse transcriptase-polymerase chain reaction; SD = standard dose.

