#### **9.2.1.5 Sensitivity Analysis of Primary Endpoint**

The analyses for the primary endpoint for the pooled analysis will be repeated for participants who received two SDs of vaccine and the second dose is SD based on randomized treatment (ie, SDSD + LDSD Seronegative ITT for Efficacy analysis set).

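### The set labelled ITT keeps the primary set's post-randomisation conditions, and no planned efficacy analysis compares all dosed participants by randomised arm

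*SAP*

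**What the plan says.** Section 5 sets the default: "All analyses will be performed by actual treatment received". It then names one exception: "For primary endpoint, a sensitivity analysis by randomized treatment assignment will be performed".

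The set for that exception is the SDSD + LDSD Seronegative ITT for Efficacy set in Table 3. It admits baseline-seronegative participants "who received two doses, planned to receive LD/SD or SD/SD or in the corresponding control group", provided that they "remain on-study 15 days after their second dose without having had a prior SARS-CoV-2 virologically-confirmed" COVID-19 infection. The same row says that they are analysed by randomised treatment, whether or not they discontinued early, "according to the intent-to-treat principle".

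Section 9.2.1.5 lists this as the only sensitivity analysis of the primary endpoint. It describes the participants as those "who received two SDs of vaccine and the second dose is SD based on randomized treatment", but cites the SDSD + LDSD set.

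Section 9.1.2.6 plans a separate secondary analysis of COVID-19 from the first dose in the Any Dose for Efficacy set. Under Table 3 that set takes randomised adults with at least one dose (efficacy groups only in COV002) and assigns them to the treatment received. Anyone given a dose of AZD1222 counts as AZD1222.

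**The concern.** Receiving dose 2, staying on study and remaining free of confirmed infection all happen after randomisation, and the vaccine can influence them. COV001, COV002 and COV003 are participant-blind, the controls differ (MenACWY or saline), and Section 6 says that dose 2 was delayed beyond a month for some participants. There is therefore room for the arms to differ in who reaches the landmark.

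The primary endpoint starts 15 days after dose 2, so some landmark conditioning in the primary analysis cannot be avoided. The difficulty is the label on its companion. A reader told that the ITT analysis agrees with the primary one would take this as reassurance about selection, which the analysis cannot give because both estimates rest on the same conditions. The row is also at odds with itself: it claims to disregard premature discontinuation, yet excludes anyone who leaves before the landmark.

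**Working it through.** The SAP gives no figure on this point to reproduce, and its power and alpha figures do not enter. The check is mainly a comparison of definitions.

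**Step 1. Definitions side by side (Table 3, Sections 9.1.1, 9.1.2.6 and 9.2.1.5).**

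| Element | Primary set (SDSD + LDSD Seronegative) | Set labelled ITT | Any Dose for Efficacy |
|---|---|---|---|
| Seronegative at baseline | yes | yes | not required |
| Second dose required | yes | yes | no |
| On study to 15 days after dose 2 | yes | yes | no |
| No earlier confirmed COVID-19 | yes | yes | no |
| Regimen | as received | as planned | any |
| Arm | as received | as randomised | as received |
| Cases counted from | dose 2 + 15 days | dose 2 + 15 days | dose 1 |

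The first two columns differ only in the regimen and arm rows. A difference between those two results can come only from participants whose planned and received treatment differ. Selection through the three shared conditions moves both results together. The third column is free of those conditions but is as treated. No column combines randomised arm with freedom from the conditions.

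**Step 2. Time before counting starts.** Days from dose 1 = dosing interval + 15.
- 4-week interval (assumed, as an example): 28 + 15 = 43 days.
- 12-week interval (start of the SAP's longest schedule category): 84 + 15 = 99 days.

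This is the window in which selection could act. It is not a measure of bias.

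**Step 3. Planning counts in Table A1.** These are August 2020 figures, floored to 100, with serostatus ignored. Any dose is about 19200 and SDSD + LDSD about 19000.
- Difference: 19200 − 19000 = 200, and 200/19200 = 1.0%.
- Range allowed by flooring: 19200 − 19099 = 101 to 19299 − 19000 = 299.

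Infections and withdrawals before the landmark are not in this figure.

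**Step 4. Illustration of sensitivity, on assumptions that are not in the SAP.** Let 20% of participants have 5-fold risk, with a true VE of 60%. Suppose a fraction d of the vaccine arm, all high-risk, fails the conditions, and nobody in the control arm does.
- Control mean risk: 0.8 × 1 + 0.2 × 5 = 1.8.
- Vaccine-arm mean risk after exclusion: m = [0.8 + (0.2 − d) × 5]/(1 − d).
- Observed VE = 1 − 0.4 × m/1.8. With no true effect, the spurious VE is 1 − m/1.8.

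| d | m | Observed VE (true 60%) | Spurious VE (true 0%) |
|---|---|---|---|
| 2% | 1.70/0.98 = 1.735 | 61.5% | 3.6% |
| 5% | 1.55/0.95 = 1.632 | 63.7% | 9.4% |
| 10% | 1.30/0.90 = 1.444 | 67.9% | 19.8% |

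If all 200 from Step 3 came from the vaccine arm under 1:1 allocation (assumed; the SAP gives no pooled ratio), d would be 200/9600 = 2.1%, close to the first row.

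Conditioning only on no earlier infection works the other way. Let the control early attack rate be q and early VE be v. Solve 0.8(1 − e^(−l)) + 0.2(1 − e^(−5l)) = q for l. The mean risk of those still uninfected is [0.8e^(−lk) + e^(−5lk)]/[0.8e^(−lk) + 0.2e^(−5lk)], with k = 1 in controls and k = 1 − v in the vaccine arm. VE is 1 − 0.4 times the ratio of vaccine to control mean risk. For q from 1% to 10% and v from 50% to 70%, observed VE runs from 59.8% down to 57.6%. The direction of any net bias is therefore not fixed either.

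**The case against.** Five points can be made for the plan.

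- **Purpose.** A reader might infer that this analysis was meant to test post-randomisation selection and fails at it. The documents do not say so. Section 5 and the Table A1 footnote give its purpose as randomised versus actual assignment, and among those who qualify it does that. This stands. The fault lies in the label and the discontinuation clause.
- **Existing cover.** A reader might also infer that early cases and dropouts are never analysed. They are: Section 9.1.2.6 counts COVID-19 from dose 1 without the three conditions, and Table A1 adds severe disease, hospitalisation, ICU and death from dose 1. As-treated assignment there does not bring back selection on dose 2, dropout or early infection; it affects only those whose actual treatment differed from the randomised one. The SAP gives no figure to suggest that they are many. This stands, and the cover is substantial though not complete.
- **Disposition tables.** Section 8.2 reports discontinuations and reasons for exclusion from each analysis set by treatment group, and Section 8.4 reports number of doses by treatment. A marked imbalance would be visible. This stands, although such tables do not show what an imbalance does to VE.
- **Different estimand.** The primary objective concerns two doses. Person-time from dose 1 answers another question and includes time before full protection, so a lower VE would not isolate selection. An unrestricted version could also take in COV001 groups planned for one dose. Both points stand and shape the fix.
- **Discontinuation clause.** It could be read as covering only those who leave after the landmark. That would make it true, but the row does not say so and calls the result intent-to-treat.

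**Conclusion.** The point holds in a limited form. The set labelled ITT is an as-randomised version of the primary landmark set. It can address misallocation and dose deviation, but not selection through the conditions that it shares with the primary set. Its discontinuation clause contradicts its own entry criteria, and the description of the set in 9.2.1.5 contradicts the set that it cites. The from-dose-1 analysis covers much of the gap, but no planned efficacy analysis compares all dosed participants by randomised arm. These conclusions rest on the text alone.

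It would go too far to conclude that the primary VE is biased. The SAP gives no data by arm on missed second doses, withdrawals or early infections, so neither the size nor the direction of any selection bias can be derived. The only guide to scale is the gap of about 1% in Table A1. The shifts in the working depend on the assumed 20% high-risk share, the 5-fold risk and one-sided exclusion.

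**What to change.** 1. In Table 3, rename the set, for example as-randomised, per-protocol landmark set. Remove the intent-to-treat claim and the clause on premature discontinuation. Carry the new name into Section 9.2.1.5 and the Table A1 footnote.
2. Add to Section 9.2.1.5 a supplementary rerun of the 9.1.2.6 model by randomised arm. Include dosed participants of the efficacy groups planned for LD/SD or SD/SD, and their controls, with person-time from dose 1. Set no condition on receiving dose 2, on reaching the Day 15 landmark or on interim infection. The restriction to baseline seronegatives may be kept, which would bring it closer to the primary population. State that this is a different estimand, and that its VE is expected to be lower because it includes time before full protection.
3. Reconcile the reference to two standard doses in Section 9.2.1.5 with the SDSD + LDSD set that it cites.

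The cost is a few lines of SAP text and one more run of a model already planned. The primary analysis, its alpha and its power are unchanged.

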## 7.6 Windowing Conventions

A windowing convention will be used to determine the analysis value for a given study visit for immunogenicity data analyses. The window definitions as following will be used for the immunogenicity.

- A window of  $\pm 14$  days from the target day is applied to the following visits: Study Days 28, 56, 90 and 182;
- A window of  $\pm 30$  days from the target day is applied to the following visits: Study Days 364;

- A window of  $\pm 42$  days from the target day is applied to the following visits: Overall post first dose + 28;

One or more results for a particular immunogenicity variable may be obtained in the same visit window. In such an event, the result with the date closest to the expected visit date will be used in the analysis. In the event that two observations are equidistant from the expected visit date, the later observation will be used in the analysis.

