## 11. IMMUNOGENICITY ANALYSIS

Immunogenicity analysis will be based on participants with data available. Summary by actual treatment for overall and by serostatus group (Seronegative, Seropositive) for analysis sets planned in [Appendix A](#).

The immunogenicity endpoints are:

- SARS-CoV-2 S, RBD antibody quantification
- Virus NAb assays against SARS-CoV-2
- Antibody seroconversion rate ( $\geq 4$ -fold increase from baseline) against SARS-CoV-2 S protein, RBD and NAb

A multiplexed immunoassay that assesses SARS-CoV-2 S, RBD, and N antigens, will be utilised to determine the antibody responses to AZD1222 vaccination. GMTs and GMFRs of these antigens may be provided at baseline and 28 days after each dose in participants for whom data are available.

Data on neutralising antibodies will be provided in the form of a pseudoneutralisation assay, with GMTs and GMFRs reported at the same timepoints as above.

The proportion of participants who have a post-treatment seroresponse ( $\geq 4$ -fold rise in titers from the day of dosing baseline value to 28 days post each dose) to AZD1222 as measured by SARS-CoV-2 binding or neutralising antibodies will also be provided, as data are available. For neutralization assays the proportion with neutralizing titres ( $> \text{LLOQ}$ ) will be generated for the primary manuscript.

As bandwidth of laboratories allows, live virus neutralisation and ELISpot data will complement the data provided. These data will be stratified by age (category 1: 18-55, 56-69, and  $\geq 70$  year-old participants for primary manuscript and category 2: 18-64 and  $\geq 65$  year-old participants), baseline serostatus and provided following validation of the assays and testing.

Descriptive statistics for GMTs and GMFRs will include number of participants, geometric mean, 95% CI, minimum and maximum. Medians, 25th quartiles and 75% quartiles may also be presented.

The GMT will be calculated as the antilogarithm of  $\Sigma (\log 2 \text{ transformed titer}/n)$ , ie, as the antilogarithm transformation of the mean of the log-transformed titer, where n is the number of participants with titer information. The 95% CI will be calculated as the anti-logarithm transformation of the upper and lower limits for a two-sided CI for the mean of the log-transformed titers.

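### Immunogenicity summaries keep S, RBD and NAb results drawn after an on-study SARS-CoV-2 infection; the likely effect is small, but an infection-censored summary should be shown beside them

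*SAP*

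**What the plan says.** Table 3 (Section 5) draws both immunogenicity sets from Any Dose for Safety. It requires the regimen or the corresponding control, and then: "Participants without at least one post baseline immunogenicity result will be excluded". The section opens with general exclusions, introduced by "The groups/participants meeting any of the conditions below will be excluded from all analysis sets". These cover non-randomised groups, earlier ChAdOx1-vectored vaccination, HIV diagnosed at study start, and children. On-study SARS-CoV-2 infection is not among them.

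Section 11 states that "Immunogenicity analysis will be based on participants with data available". It summarises by actual treatment, overall and by serostatus. The assay is described in terms of vaccine response: "A multiplexed immunoassay that assesses SARS-CoV-2 S, RBD, and N antigens, will be utilised to determine the antibody responses to AZD1222 vaccination". Seroresponse is likewise described as a response to AZD1222: "The proportion of participants who have a post-treatment seroresponse", defined as at least a four-fold rise. The reporting times named are baseline and 28 days after each dose.

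Where several results fall in one window, Section 7.6 says that "the result with the date closest to the expected visit date will be used in the analysis". Table 5 lists illness visits among the immunogenicity windows.

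The seronegative two-dose efficacy sets in Table 3 do address earlier infection. Their participants must "remain on-study 15 days after their second dose without having had a prior SARS-CoV-2" infection confirmed virologically.

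**The concern.** Natural infection raises the same three readouts that Section 11 uses to describe the vaccine: S, RBD and neutralising antibody. Splitting by baseline serostatus deals with infection before the first dose but not after it. In the AZD1222 arm, a titre raised by infection is averaged in as vaccine response. In the control arm, where participants received MenACWY or saline, nearly every four-fold rise would be an infection, and nothing in the table would say so.

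The plan recognises on-study infection elsewhere and will hold the data. The efficacy sets screen for it, and Section 9.1.2.18 splits the nucleocapsid endpoint by PCR result. That split covers N antibody only, not S, RBD or NAb.

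**Working it through.** **Step 1: is there any rule that removes a post-infection sample?**

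| Place in SAP | What it governs | Acts on S, RBD or NAb results after infection? |
|---|---|---|
| Section 5, general exclusions | all sets | No |
| Table 3, immunogenicity sets | regimen and one post-baseline result | No |
| Section 7.2 | serostatus at baseline | Only infection before dose 1 |
| Section 7.3 | value before dose 2 as baseline for change from dose 2 | Partly, for post-dose-2 fold rise |
| Section 7.6, Table 5 | choice of sample | No; nearest date only |
| Section 9.1.2.18 | N antibody by PCR result | No |
| Section 11 | S, RBD and NAb summaries | No |

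Table 5 gives illness visits their own windows, but no sentence stops an illness-visit sample from also filling a Day 28 slot (Days 14-42).

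**Step 2: which summaries are exposed?**
- GMTs at 28 days after each dose.
- GMFR and seroresponse at 28 days after dose 1.
- After dose 2, if the pre-dose-2 value is the baseline, fold rise largely absorbs infection between doses. It does not absorb infection after dose 2, and GMTs are not protected at all.
- The visit Overall post first dose + 28, if it is reported. Table 5 gives it Days 14-104. (Section 7.6's ±42 days around Day 56 would give 14-98.)

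**Step 3: scale.** The plan gives no immunogenicity estimate, so there is no figure to reproduce.

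Inputs from the SAP:
- D = 105 SD/SD cases at the primary analysis, and true efficacy 60% (Section 4.1).
- N of about 15600 for SD/SD (Table A1).

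Assumed:
- 1:1 allocation.
- Infection multiplies a participant's titre by k = 5 to 10.
- Cases are spread evenly over participants with immunogenicity data.
- Every case precedes the sample.

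Cases by arm, with relative risk 0.4:
- AZD1222: 105 × 0.4/1.4 = 30. Share f = 30/7800 = 0.38%.
- Control: 105 × 1/1.4 = 75. Share f = 75/7800 = 0.96%.
- Both arms: 105/15600 = 0.67%.

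If a share f of results is raised k-fold, the geometric mean is multiplied by k^f:

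| Arm | f | k = 5 | k = 10 |
|---|---|---|---|
| AZD1222 | 0.38% | 1.006 | 1.009 |
| Control | 0.96% | 1.016 | 1.022 |

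Seroresponse can rise by at most f: about 0.4 percentage points in AZD1222 and about 1 in control.

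**Step 4: sensitivity to the assumptions.**
- Widening k to 4-100 gives 0.5-1.8% for AZD1222 and 1.3-4.5% for control.
- Table A3 shows about 19200 in its SDSD row. With that N the shares fall to 30/9600 = 0.31% and 75/9600 = 0.78%.
- If 2% of results were post-infection, the factor would be 5^0.02 = 1.033 to 10^0.02 = 1.047.

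**The case against.** The strongest reply is that an all-data summary is a defensible choice and that censoring has its own bias. Infection occurs after randomisation and is affected by treatment. Dropping post-infection results removes more controls than vaccinees. If weak responders are infected more often, it also removes weak vaccine responses, so the filtered GMT could be biased upward as well. This stands, and it is why the censored summary should accompany the all-samples summary rather than replace it.

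Other parts of the reply also stand. Results are shown by arm, so the control column displays the infection background. N seroresponse is tabulated by PCR result on the same sets. Country is a planned subgroup. The efficacy sets are an imperfect precedent, since they screen for infection because their endpoint is a first case. None of this separates infection from vaccination within the S, RBD and NAb summaries.

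Two stronger readings are tempting, but the document does not support them:
- **Bias that grows at later visits.** Table 5 has windows to Day 364, so a reader might infer this. Section 11 names only baseline and 28 days after each dose for these readouts, and Table 5 also serves the nucleocapsid endpoint.
- **Inflation of 8-26%.** This needs 5-10% of participants infected before the sample (5^0.05 = 1.084; 10^0.10 = 1.259). Nothing in the plan points to such a share, and its own case count gives 1% or less per arm.

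Nor does the plan set up formal comparisons that this could overturn. Section 11 is descriptive, and dose schedule is only an optional subgroup.

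**Conclusion.** The gap is real and follows from the definitions as written: no rule removes, censors or flags S, RBD or NAb results drawn after an on-study infection. Under the stated assumptions, the AZD1222 GMT is raised by about 0.6-0.9%, the control GMT by about 1.6-2.2%, and control seroresponse by up to about 1 percentage point.

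These figures are for scale only. They could be too low, because the 105 cases leave out asymptomatic infections and everything before 15 days after dose 2, which is most of the risk period for a sample 28 days after dose 2. They could be too high, because the 105 include cases arising after that sample.

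The main defect is interpretive: control seroresponses that are mostly infections appear without that label, and the seronegative row for AZD1222 is not purely vaccine response. Section 2.2 makes humoral immunogenicity a secondary objective, conditional on data being available, so this is a low-priority correction.

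**What to change.** In Table 3 and Section 11:

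1. For baseline-seronegative participants, add a summary of S, RBD and NAb (GMT, GMFR and seroresponse) that drops any result dated on or after the first PCR-positive date or first N-positive result, whichever is earlier. Keep the participant's earlier samples.
2. Show it by arm beside the all-samples summary, with the number of results dropped in each arm.
3. In Section 7.6, state that illness-visit samples may not fill a scheduled-visit window.

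The cost is a few sentences and a date filter. PCR dates are already needed for the efficacy endpoints, and N is part of the multiplex assay, although Section 9.1.2.18 makes the N summary conditional on data being available. The downsides are slightly fewer samples in the censored summary and the conditioning on a post-randomisation event. Showing both summaries lets the reader see how far they differ.
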